### Sample size and power analysis

We anticipate including > 50 clinics and approximately 395,000 unique behavioral health patients across three sites over a 2.5-year period, leading to over 1 million patient visits. We project that approximately 4–5% of patients will be identified as high risk and thus eligible for the intervention. Utilizing a stepped-wedge cluster randomized controlled trial design, with > 50 clinics randomly assigned across three waves, we will assess the primary outcome, suicide attempts, at 90- and 180-days post-intervention. Given an anticipated suicide attempt rate of 0.6% (*n* = 2,370) within 90 days of a visit, a 0.01 intraclass correlation coefficient within waves, we expect to achieve more than 80% power (2-sided *p* <.05) to detect an effect size corresponding to a 1.5% absolute difference in suicide attempt rates [47–49].

### Analysis plan for effectiveness outcomes

We will analyze outcomes, for both: (1) unique patients, defined as those new to the study sample without a visit in the past three months, and (2) unique visits, where each health care encounter is considered separately, allowing for multiple visits per unique person, given that patients may be screened or identified as at-risk at multiple visits.

Only study biostatisticians will have access to the final trial datasets. We will begin with descriptive analyses of the study sample, including patient demographic characteristics, encounters, history of past-year suicide attempt, and current mental health diagnoses by exposure group. Descriptive analyses will also examine each of the individual identification and recognition measures using health system records, stratified by exposed (intervention) versus unexposed (control) periods. We will calculate the clinic/cluster sizes for each phase of implementation and clinic/cluster characteristics by exposure period to assess balance across the study period. Standard chi-square tests and t-tests will be used to compare variation in each outcome variable between exposure groups, and in each unique phase of implementation. We will then plot change in both counts and proportions of each individual outcome graphically by study exposure period.

Generalized Linear Mixed Models (GLMMs) with logit link function will be used to assess categorical outcomes (identification and recognition, separately, defined as yes/no) to study the effect of the intervention on identification and recognition. The results will be presented as odds ratios (OR) with 95% CIs. We will analyze the frequency of events identified through PHQ-9 (identification), recognized through the C-SSRS (recognition), or both combined. Additionally, GLMMs with a log link function will be used to separately assess the effects on identification and recognition by modeling the count of identified or recognized patients. The model will include the intervention (yes/no) as an independent variable to assess its effect while accounting for clustering and potential confounders. Among visits where individuals are identified or recognized as being at risk, we will further investigate factors influencing these outcomes, including patient demographics and clinical characteristics. The results will be presented as relative risk (RR) with 95% CIs. In these analyses, clusters will be analyzed according to their randomized crossover time. Models will include a random effect for cluster and a fixed effect for each phase, and will adjust for age, sex, race/ethnicity and cluster/clinic terms (i.e., secular trend). These models are optimal and commonly used for studies implementing stepped wedge cluster randomized trial designs [31, 32, 50]. All analyses will also adjust for time, given that the ratio of exposed clinics increases over time, and calendar month to account for seasonality of suicide attempts. Given that patients may be screened or identified as at-risk multiple times, the frequency of visits during the follow-up period will be adjusted in the model as well. In additional analyses, the model will account for cluster effects by clinic and correlation between repeated measurements for the same patient over time.

These models will also be used to test mediators/mechanisms, given that we hypothesize that identification alone will not reduce suicide outcomes but rather increase the number of people receiving suicide intervention, which could lead to improvement (i.e., decrease) in suicide outcomes. Mechanisms include interaction with the alert and initiation of assessment, which starts the outpatient care pathway. We will also stratify analyses by health system site, and test for mental health diagnoses and prior suicide attempts as moderators. Importantly, we will exclude ‘training’ months for each phase of clinic implementation from the main analyses, since clinicians and patients may be partially exposed as the models are implemented and clinicians trained. In a secondary set of analyses, we will explore potential heterogeneity in treatment effects between clinics. Here we will conduct additional analyses to test within cluster comparisons of exposed and unexposed periods.

To examine the effectiveness of a suicide risk model on health service engagement and suicide attempt outcomes, we will start with similar descriptive and GLMMs analyses proposed previously for identification and recognition. The analyses here will focus on each unique health service engagement (supportive and crisis encounters separately) and suicide attempt outcomes, stratified by exposed (intervention) versus unexposed (control) groups. Suicide attempts will be captured by health system records using ICD-10 diagnosis codes occurring within the same 90-day and 180-day time periods. We will also use a Kaplan-Meier method and Cox-proportional hazards models to examine time-to-event for health service engagement and suicide attempts, with statistical adjustment for clinical and demographic factors. Individuals will be censored at the time of death or at 180 days past the index visit. We will again add terms for calendar month as well as site to account for variation by season and health system.

Finally, we will separately examine the impact of health care engagement and exposure to ZS evidence-based interventions as mediators of suicide attempt and use of crisis services. We will estimate direct and indirect effects in our longitudinal settings using our previously proposed GLMMs [51]. Specifically, we will test the effect of the intervention (risk model study group, yes/no) on behavioral health service engagement (yes/no within 7 and 14 days via path ‘*a’*) and the effect of behavioral health service engagement on suicide attempt outcome (yes/no within 90 and 180 days via path ‘*b*’). The residual effect of the intervention unaccounted for by behavioral health service engagement will be tested via path ‘*c*’. We will also test a separate path model of exposure to documented suicide prevention interventions and their impact on suicide attempt outcomes using the same modeling approach. These models will include both individual documented supportive outpatient interventions for suicide and multiple interventions bundled together; we will also repeat these analyses for crisis services outcomes.

We will address missing data using multiple imputation or inverse probability weighting, depending on the nature and extent of missingness. Additionally, if the proportion of missing data is substantial, we will conduct sensitivity analyses to assess its potential impact on our findings.

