**Methods:**

This hybrid type I effectiveness-implementation pragmatic clinical trial will test a suicide risk identification model in behavioral health clinics at three large health systems. Local decision-makers will determine implementation specifics at each site. Clinics within each health system will be randomized to determine order of implementation. A stepped-wedge design using repeated measures pre/post-implementation maximizes statistical efficiency and power with fewer participants compared to a parallel design while allowing all clinics to participate. A pre-implementation period will serve as the baseline. The primary outcome will be the rate of suicide attempt per 1000 visits at 90- and 180-days following a behavioral health visit in which an individual was identified by the suicide risk model compared with the baseline period (no use of suicide risk model). Secondary outcomes include identification of suicide risk and recognition of individuals at risk for suicide (e.g., completed risk assessment), both compared to the baseline period. Generalized linear mixed models will be used to account for clustering within clinics and repeated measures over time, adjusting for relevant covariates to estimate the effect of the suicide risk model on outcomes. Implementation outcomes, including system-level determinants and clinician acceptance and use of the suicide risk model, will also be measured.

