## Methods

### Objectives and hypotheses

The current study will test the implementation of the MHRN suicide risk model in behavioral health clinics to facilitate identification, recognition, and engagement in supportive suicide prevention services among individuals estimated to be at risk for suicide. The study’s main aim is to examine the effectiveness of a suicide risk model on fatal and non-fatal suicide attempts (primary outcome). The secondary outcome analyses examine the following questions: Are patients who receive care in the behavioral health intervention clinics more likely to be referred to and receive supportive outpatient behavioral health services than patients in usual care clinics? Are they more likely to receive supportive services sooner after risk recognition than they would have before the risk models were used, or earlier than patients in usual care clinics? Are they less likely to require crisis services and less likely to attempt suicide? Specifically, we will test the hypothesis that the risk model will lead to a reduction in suicide attempts (primary outcome) and an increase in referrals to, and receipt of, supportive outpatient services (secondary outcome).

In secondary analyses, we will determine whether implementing a suicide risk model into a suicide prevention care model improves identification of patients at risk for suicide attempt (suicide screening practices); that is, whether the enhanced identification using a risk model improves upon self-reported risk screening relied upon in usual care. Specifically, does the risk model (intervention) identify additional patients for screening who would not be identified in the course of usual care? How many additional patients are recognized (complete a risk assessment)? We hypothesize that the risk model may identify people who miss or refuse screening, deny risk because they do not believe themselves to be at risk or feel ambivalent, or deliberately conceal their risk. We will test the hypothesis that the suicide risk model implementation will improve identification and recognition of patients at increased risk of suicide attempt compared to usual care.

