### Study measures and effectiveness outcomes

The primary outcome measure is fatal or non-fatal suicide attempt (binary yes/no) within 90 or 180 days of a behavioral health visit as measured using diagnosis codes for intentional self-harm (International Statistical Classification of Diseases and Related Health Problems, Tenth Revision [ICD-10] codes X60-X84; Y87.0). Suicide deaths will be ascertained from government mortality records. The denominator will be the total number of visits to behavioral health clinics and the numerator will be reported as the number of suicide attempts per 1000 visits. In addition to the primary outcome, we will examine proximal outcomes and crisis utilization measures. Proximal outcomes include measures of engagement with services documented in the EHR within the observation period. These are defined as: evidence-based suicide prevention interventions (safety planning, lethal means counseling, or caring contacts) on or after the risk identification (index) encounter, an outpatient encounter (includes telephone, virtual, and office visits) by a behavioral health clinician or psychiatrist subsequent to the index encounter, any contact with behavioral health within seven or 14 days of the index visit (includes phone calls, letters, patient portal messages, or other caring contacts in addition to encounters described above), frequency of contacts, latency to next encounter after index, and persistence in psychotherapy defined as no gap in psychotherapy visits > 90 days during the observation period. Crisis utilization measures include any encounters in the emergency department or inpatient stays subsequent to the index encounter within 90 days and 180 days.

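### The primary outcome has two unranked windows (90 and/or 180 days) and an unsettled unit; if either window can win at 0.05, the false-positive rate is about 7-10%

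*Protocol article*

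**What the plan says.** **Hypothesis.** Objectives and hypotheses: "the risk model will lead to a reduction in suicide attempts (primary outcome").

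**Window.**
- Abstract, Methods: "The primary outcome will be the rate of suicide attempt per 1000 visits at 90- and 180-days following a behavioral health visit".
- Study measures and effectiveness outcomes, where the definition reads: "The primary outcome measure is fatal or non-fatal suicide attempt (binary yes/no) within 90 or 180 days of a behavioral health visit".
- Sample size and power analysis: "we will assess the primary outcome, suicide attempts, at 90- and 180-days post-intervention".

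The first and third join the windows with 'and', the second with 'or'. None says which window decides.

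**Unit.** The Abstract and the measures section both express the primary outcome per 1000 visits, and the measures section makes total behavioral health visits the denominator. The sample size section gives a 0.6% attempt rate within 90 days and 2,370 events, for about 395,000 unique patients and over 1 million visits. The analysis plan then says "We will analyze outcomes, for both: (1) unique patients, defined as those new to the study sample without a visit in the past three months". It lists unique visits as the second unit and does not rank the two.

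**Level.** It appears once, in the power sentence: "we expect to achieve more than 80% power (2-sided *p* <.05").

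**Further analysis of attempts.** "We will also use a Kaplan-Meier method and Cox-proportional hazards models to examine time-to-event for health service engagement and suicide attempts".

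**The concern.** The trial is meant to establish whether the risk model reduces suicide attempts. That needs one stated test, or a stated rule for combining several. Here the time window is open, and the sections do not agree on the unit of analysis.

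The choices are not interchangeable. An effect that fades after three months could show at 90 days and not at 180; one that builds slowly could do the reverse. The visit analysis counts frequent attenders many times, whereas the unique-patient analysis admits a person only when there has been no visit in the previous three months. The two analyses therefore weight and cover different people. Two analysts following the text in good faith could report different primary results from the same data, and a result on whichever window happened to reach significance would carry more than a 5% risk of error.

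**Working it through.** **1. Reproduce the plan's event count and find its unit.**
Inputs (sample size section): rate 0.6%, 395,000 unique patients, over 1 million visits.
- On patients: 0.006 × 395,000 = 2,370. This matches the stated count exactly.
- On visits: 0.006 × 1,000,000 = 6,000 or more. This does not match.

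So the power statement counts patients, while the outcome is defined on visits. It settles neither point cleanly: it favours 90 days as the window, because only a 90-day rate is given, but it uses the other unit. Whether its power figure can itself be reproduced is a separate question on which nothing below depends.

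**2. Two windows, one unit.**
Assume no true effect, each window tested at |Z| > 1.96, and success on either counted as a positive trial. With correlation r between the two statistics:

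false-positive rate = 1 − P(|Z₁| ≤ 1.96 and |Z₂| ≤ 1.96)

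If independent, this is 1 − 0.95² = 9.75%. Otherwise it comes from the bivariate normal distribution:

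| r (assumed) | rate |
|---|---|
| 0 | 9.8% |
| 0.5 | 9.1% |
| 0.71 | 8.3% |
| 0.8 | 7.8% |
| 0.9 | 7.0% |

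The document gives no correlation. The value 0.71 comes from treating the 90-day event as nested in the 180-day event, with 0.6% by day 90 (stated) and 1.2% by day 180 (assumed):

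r = √[0.006 × 0.988 / (0.012 × 0.994)] = √0.497 = 0.705

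These rates count errors in either direction. Counting only false claims of benefit, against a nominal 2.5%, the rate is 1 − 0.975² = 4.9% if independent, 4.5% at r = 0.5 and 3.5% at r = 0.9.

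**3. Two windows and two units (conditional).**
This applies only if a patient-level result could also carry the primary claim. There are then four tests, with correlations taken as (between windows) × (between units), all assumed:
- independent: 1 − 0.95⁴ = 18.5%
- both 0.5: 16.1%
- both 0.7: 13.7%
- both 0.8: 12.0%
- both 0.9: 9.8%
- 0.71 between windows with 0.5 to 0.9 between units: 14.8% to 11.5%

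**4. What a rule would do.**
- One named contrast at 0.05, or 180 days tested only after success at 90 days: 5.0%.
- Both windows must succeed: no more than 5%.
- Equal Bonferroni split over two windows: 0.05 / 2 = 0.025 each.

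**The case against.** **The unit is already stated.** The Abstract and the measures section define the primary outcome per visit, and unique-patient denominators are specified only for the secondary outcomes, identification and recognition. The analysis plan's sentence on two units is a general one, and the reason it gives is repeated screening and identification. Most of this stands. A reader might infer four equal primary tests and an error rate of 12-16%; the documents do not support that as the headline, because a patient-level result does not meet the stated definition. Some ambiguity does remain: the event count is patient-based, the two units are unranked, and the plan carries the same modelling approach over to suicide attempts.

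**Joining the windows with 'and' may mean both must succeed.** Under that reading there is no inflation across windows. But no section says so, the measures section uses 'or', and the power statement gives a rate for 90 days only.

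**Testing each window at 0.05 is an inference.** It is. The level appears once, in a power sentence. Nothing says that one success is enough, and nothing rules it out.

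**Multiplicity rules belong in an analysis plan that is not shown.** A missing hierarchy would not, on its own, be a point against a condensed article. The conflict over the windows and the mismatch of units are statements in this article, however, and need correcting here whatever a later plan says.

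**The Cox model.** It might be read as one more primary test. The text adds it after the mixed models and never presents it as primary, so it is not counted.

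**Conclusion.** The point holds in limited form. The article gives the primary outcome two unranked windows, joined differently in different sections, with one 2-sided 0.05 level and no rule for which window decides. If either may win, the false-positive rate is about 7-10% instead of 5%. That rests on two assumptions: separate tests at 0.05, and a correlation between 0.9 and zero.

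The unit inconsistency is secondary. Visits are the defined unit, patients are the unit behind 2,370, and both are analysed without ranking. The larger range of about 10-18.5% (12-16% for correlations of 0.8 to 0.5) applies only if a patient-level result could also be claimed as primary, which the outcome definition speaks against. Nor does the text show that an inflated claim is intended. It shows that the deciding test has not been fixed. This should be corrected before analysis, but it does not undermine the design.

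**What to change.** In the measures, sample size and analysis sections, and in the Abstract's wording where it can still be changed, state that one contrast decides the trial. A choice that follows the article's own text is the 90-day attempt outcome (the window in the power statement), analysed on visits (the unit in the outcome definition), from the intervention term of the generalized linear mixed model at 2-sided 0.05.

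For 180 days, choose one rule and write it down:
- test it on the same unit only if the 90-day result is significant;
- require both windows to succeed; or
- split alpha, for example 0.025 each.

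Label the unique-patient analyses and the Kaplan-Meier and Cox analyses as supportive, with no claim of effectiveness from them alone. Restate the basis of the power calculation in the chosen unit, and make the wording on the windows the same throughout.

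The cost is a few sentences before the data are analysed, plus the restated power basis; no new data are needed. With the sequential rule, a result significant only at 180 days or only in the patient-level analysis could no longer be claimed as the primary finding. Requiring both windows to succeed costs power, and splitting alpha costs some power on each window.

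### The unadjusted chi-square and t-tests of outcomes by exposure group ignore clinic clustering and calendar time, so their p-values would not hold the 5% level; the GLMM inference is unaffected

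*Protocol article*

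**What the plan says.** All of this is in the Protocol article, Analysis plan for effectiveness outcomes, unless another section is named.

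- The section opens with a descriptive step: "We will begin with descriptive analyses of the study sample". Within that step, "Standard chi-square tests and t-tests will be used to compare variation in each outcome variable between exposure groups", and likewise in each implementation phase. The step ends with plots of counts and proportions.
- Effect estimates come next, from GLMMs with a random cluster effect, a fixed phase effect, patient covariates and calendar month. They are reported as odds ratios or relative risks with 95% intervals. The section says that all analyses adjust for time, "given that the ratio of exposed clinics increases over time".
- For service engagement and suicide attempts, "we will start with similar descriptive and GLMMs analyses proposed previously for identification and recognition".
- Sample size and power analysis assumes a 0.6% attempt rate within 90 days, 395,000 patients, more than 50 clinics in three waves, and "a 0.01 intraclass correlation coefficient within waves".

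**The concern.** The tests are applied to outcomes and compare exposure groups, so each is a test of the intervention contrast and not a check of baseline balance. Because the descriptive step is repeated for suicide attempts, the natural reading is that they reach the primary outcome.

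A standard chi-square or t-test assumes independent observations. Clinics are the randomized units here, and the plan itself assumes a non-zero ICC. The visit-level analysis adds several visits per patient. In a stepped wedge, moreover, control time is mostly early and intervention time mostly late, so any secular change appears as a difference between exposure groups. A test within one phase would remove most of the time confounding but would still ignore clustering.

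What is at stake is a set of p-values that can be small with no effect of the risk model. Secular change is plausible: the Background reports national suicide rates rising, then falling 5% in two years, then returning near their peak, and Study settings describes screening practice that has kept changing.

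**Working it through.** **Plan's own figure.** 0.006 × 395,000 = 2,370 patients with an attempt, as stated in Sample size and power analysis.

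**Inputs from the article.** Rate 0.6%; 395,000 patients over 2.5 years; three waves, three to six months apart; clinics 10 + 4 + 39 = 53, serving about 50,000, 60,000 and 58,000 patients a year (Study settings).

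**Assumptions.** Ten three-month periods; waves cross at periods 4, 6 and 8 (six-month spacing), so they are exposed for 70%, 50% and 30% of the time. The ICC of 0.01 is stated within waves; it is applied here between clinics, with smaller values beside it. No intervention effect; two-sided 5% test.

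**1. Clustering only, no trend.** With exposed fraction x in a clinic, the exposed-minus-unexposed difference weights that clinic's own rate by (2x − 1). The mean of (2x − 1)² over the waves is (0.16 + 0 + 0.16)/3 = 0.1067. Relative to the variance that the chi-square test assumes, the true variance is

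V = 1 + ICC × 0.1067 × (Σm²/N),

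where m is clinic size and N = 395,000. The false-positive rate is P(|Z| > 1.96/√V).

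- Equal clinics: Σm²/N = 395,000/53 = 7,453.
- Sizes proportional to site volume: N × (50/168)/10 = 11,756, N × (60/168)/4 = 35,268 and N × (58/168)/39 = 3,497 per clinic, so Σm²/N = 17,302.

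| ICC (clinic) | V, equal | Rejects, equal: formula / simulated | V, site-proportional | Rejects, site-proportional: formula / simulated |
|---|---|---|---|---|
| 0.01 | 8.95 | 51% / 51-52% | 19.46 | 66% / 62% |
| 0.001 | 1.79 | 14% / 13-14% | 2.85 | 25% / 25% |
| 0.0001 | 1.08 | 6% / 6% | 1.18 | 7% / 7% |

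The simulated columns use 4,000 null trials per scenario at the 0.6% rate, with gamma-distributed clinic rates. At a 5% rate, nearer to an identification outcome, the simulation gives 50-66% at ICC 0.01 and 14-26% at 0.001. A simulation with crossovers at quarters 5, 7 and 9 gives 61% and 25%.

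**2. Trend only, ICC 0.** The mean exposed period is (7×7 + 5×8 + 3×9)/15 = 7.73 and the mean control period is (165 − 116)/15 = 3.27. The gap is 4.47 of the 9 steps from first to last period, so about 0.496 of the total log change becomes a spurious log rate ratio. With about 1,185 events per group, SE = √(2/1,185) = 0.0411.

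- 10% total fall: 0.496 × ln 0.90 = −0.0523 (rate ratio 0.949), z = 1.27, rejection 25% (simulated 25%).
- 10% total rise: 0.496 × ln 1.10 = 0.0473 (rate ratio 1.048), z = 1.15, rejection 21% (simulated 21%).
- 5% total fall: z = 0.62, rejection 10% (simulated 9%). A 5% rise gives 9% (simulated 10%).

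**3. Accounting for clinic and period.** In the equal-clinic layout, with fixed clinic and period effects and clinic-robust standard errors as a stand-in for the planned model, the false-positive rate is 4.5-5.8% across ICC 0 to 0.01, with no trend or a 10% fall (3,000 runs each).

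Within-patient correlation between visits was not simulated; it would tend to increase the inflation.

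**The case against.** The best defence is that these tests belong to a preliminary step labelled descriptive, and that the article assigns effect estimation to GLMMs with cluster, phase and time terms; the abstract names only those models. This stands. A reader might infer that the primary analysis is invalid, and the article does not support that. Nor does it say that the p-values will be published beside the model results, and no calculation here shows the two pointing in opposite directions.

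The largest figures also depend on a strained input. The ICC of 0.01 is stated within waves. Read as between clinics at a 0.6% rate, it implies a clinic standard deviation of √(0.01 × 0.006 × 0.994) = 0.77 percentage points, larger than the mean itself. Smaller values are quite possible, and at 0.0001 without a trend the inflation is negligible. This stands too, and is why a range is given.

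The sentence promising time adjustment for all analyses sits among the model descriptions and could be read as covering models only. That would soften the contradiction but leave the tests unadjusted. Identification and recognition are aggregated to the patient, so repeated visits are a problem only for visit-level comparisons.

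A reader might extend the criticism to the time-to-event work ("We will also use a Kaplan-Meier method"). That does not follow: the curves are paired with adjusted Cox models, calendar-month and site terms are added, and no log-rank test is named.

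The defence does not show that the tests are needed. A descriptive step has no use for p-values that ignore the design.

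**Conclusion.** The concern holds for the preliminary tests and goes no further. As written, the plan commits to outcome tests that ignore the randomized unit and, for the overall comparison, calendar time, against its own statement on time adjustment. This is not a detail left to a statistical analysis plan, since the article names the tests.

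At a 0.6% rate and 395,000 patients, the actual level of a nominal 5% test is about 50-65% at a clinic-level ICC of 0.01, 13-26% at 0.001 and 6-7% at 0.0001 without a trend, and about 10-25% with no clustering but a 5-10% total secular change. The direction is certain wherever there is clustering or trend. The size rests on the assumed clinic-level ICC, clinic sizes, crossover times and trend. The GLMM-based primary inference is not affected. The point should be corrected, at moderate priority.

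**What to change.** In Analysis plan for effectiveness outcomes, replace the sentence on chi-square and t-tests of outcomes with a statement that counts and proportions will be tabulated by exposure and calendar period without p-values. Add that every between-exposure test, for suicide attempts as for the other outcomes, comes from the GLMMs with clinic and period terms. The later reference to similar descriptive analyses then carries no tests with it. The time-to-event text needs no change on this account.

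The cost is wording only. It needs no new data and removes some analysis work.
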